#### Step four: Expelling and clearing pathogenic factors

GB 40, Zulinqi (GB 41), and the sole of the foot will be massaged with major thenar kneading manipulations for three passes beginning with soft then more penetrating kneading movements from ankle GB 40, 41 to the plantar surface of the foot. Further treatment of the foot will include shaking manipulation and rotation to the ankle. To further generate Qi flow and clear pathogenic factors, toe rotation and pulling will be followed by rubbing of Shangqiu (SP 5) until the participant reports a warm sensation over the medial malleolus of the ankle.

### The placebo massages

The same therapist will provide 6 weekly 25-min placebo massage sessions to participants in the placebo group. These sessions will include an assessment of the affected extremity's legs and toes for lesions and broken skin to avoid them during the massage. The provider will perform an open hand technique of gentle foot and toe rubbing without any point stimulation or other TCFM techniques.

### The TCFM/placebo massage therapist

Two massage therapists in this trial will have Diplomate in Asian Body Works and a certified Chinese massage therapist. The two must have more than 2 years of clinical experience in this field. The two therapists will deliver both TCFM and placebo massage to all participants in both groups. The two therapists will go through a 4-h training with the PI before the commencement of the trial to familiarize the therapists with the trial protocol. After the training, the two therapists must pass an exam in which they must verbally recite the protocol and physically demonstrate each technique to the PI.

### Safety

TCFM is generally safe with the possibility of rare adverse events that might include mild discomfort, soreness, and slight bruising during or after a session (32). The safety measures will include assessment and treatment with monitoring of responses that enable the therapist to adapt the treatment to patient needs. Assessment will include skin inspection of the legs, feet, and toes for lesions, indurations, or damage. The therapist will avoid massaging the areas of skin breakage. Participants will be encouraged to verbalize experiences of increased pain, increased sensitivity in their feet, and additional discomforts of tenderness, nausea, sweating, skin rashes, or extreme fatigue. If the participants complain of increasing pain the therapist will provide more gentle therapy. The therapist will assess any unfavorable participant reactions. The therapist will carefully document these events in the case report form. To avoid the spread of infectious agents, The massage therapist will don latex or nonlatex (for those who are allergic to latex) gloves while performing the massage and perform hand hygiene after each session.

### Adherence

The participant will be reminded about their appointment by text message 1 day before their scheduled session to improve adherence to the trial. Participants' parking will be reimbursed. Subway tokens will be provided. If a participant has difficulty coming to the site, the researcher and the therapist will go to his/her home.

### Data collection

Two outcome assessors will be trained with the trial data collection protocol by the PI prior to any data collection.

#### Sociodemographic, health, and lifestyle information

Participants' sociodemographic, health, and lifestyle information will be collected using a standardized self-report questionnaire designed for this trial. Information will be collected at the first visit *via* an iPad or paper format before randomization occurs. The questions include age (years), gender (male or female), ethnicity (Mexican Americans, other Hispanics, non-Hispanic White, or non-Hispanic Black), education (below high school, high school graduate, or some college or above), domestic partner status (living with a partner or not), employment status (employed or not), alcohol use (number of standard drinks per day), smoking status (never smokers, former smokers, and current smokers), body mass index, and depressive symptoms. One standard drink contains 14 grams of pure alcohol (40). The Patient Health Questionnaire (PHQ-9) score will be used to indicate depressive symptoms (41). If the participants cannot read the questions by themselves, the interventionist will read the questions to them. Participants' height and weight will be measured for the calculation of body mass index.

#### Primary outcome

PN-related pain, lower extremity functioning, and health-related quality of life will be collected at the first visit after consenting before randomization (baseline). This information will be collected again at their sixth visit after the TCFM/placebo massage (immediate impact) and 12 weeks after the competition of the trial (long-term effect).

1) The Short Form-McGill Pain Questionnaire-2 (SF-MPQ-2) will be used to measure PN-related pain (42). SFMPQ-2, consisting of 22 items from the McGill Pain Questionnaire (MPQ), can reflect both neuropathic and non-neuropathic pain. Each descriptor is ranked from 0 to 10 (0 indicates none; one indicates mild; ten indicates the worst pain possible). Total pain is the average of all 22 items, ranging from 0 to 10. The correlation of SFMPQ-2 with MPQ has been demonstrated.2) Lower extremity functioning will be measured by the Lower Extremity Functional Scale (LEFS) (score range 0–100) (43). A higher score indicates better lower extremity functioning. The LEFS has strong tes*t-*retest reliability, cross-sectional construct validity, and internal reliability (44). It was demonstrated that it could accurately identify changes in lower extremity musculoskeletal conditions in patients that are clinically significant (45).3) Health-related quality of life will be measured by the Medical Outcomes Study Questionnaire Short Form 36 Health Survey (SF-36) (score range 0–100) (46). A lower score indicates more disability, and a higher score indicates less disability. According to prior studies, the SF-36's reliability score was higher than 0.80 (46, 47).

The secondary outcomes include (1) recruitment and completion rate (No. of referred, No. of eligible, No. of enrolled, No. of withdrawals, trial recruitment rate, and trial completion rate), (2) participant safety (No. and severity of adverse events), (3) treatment adherence (average time of each message session, No. of completed sessions, and No. of missed sessions) and compliance (No. of participants completing the trial following the initial group assignment). Adverse events will be recorded by the therapists in the notes. A published systematic review of the negative effects of massage therapy in the context of pain found the following adverse but rare events which the therapists will be instructed to watch out for, including disc herniation, soft tissue trauma, neurologic compromise, spinal cord injury, vertebral artery dissection, bone fracture, hematoma or hemorrhagic cyst, syncope, cauda equina syndrome, pain, and dislocation (32).

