**Outcomes:**

The primary outcomes, measured at baseline, end of TCFM/placebo, and twelve weeks after, include (1), lower extremity pain, (2) lower extremity functioning, and (3) health-related quality of life. The secondary outcomes, measured throughout the trial process, include (1) recruitment and completion rate (No. of referred, No. of eligible, No. of enrolled, No. of withdrawals, trial recruitment rate, and trial completion rate), (2) participants' safety (No. and severity of adverse events), (3) treatment adherence (average time of each message session, No. of completed sessions, and No. of missed sessions), and (4) compliance (No. of participants completing the trial following the initial group assignment).

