## Materials and methods

### Ethical approval

The University of Houston-Downtown Committee for the Protection of Human Subjects approved the proposed trial of this protocol after conducting an ethical review. Prior to being enrolled in the trial, participants will be fully informed regarding the possible risks involved, the informed consent process, confidentiality, and secure data storage. Participants will be informed that although TCM is generally safe, mild discomfort, soreness, and slight bruising may appear at or after a session. Severe but very rare adverse events include disc herniation, soft tissue trauma, neurologic compromise, spinal cord injury, vertebral artery dissection, bone fracture, hematoma or hemorrhagic cyst, syncope, cauda equina syndrome, pain, and dislocation (32). Participants will be informed that their decision of whether to participate in this trial will not affect any health or education service they receive at present or in the future. Participants will be guaranteed that they can leave the trial at any time without providing a reason or leading to any consequences. Oral and written informed consent will be obtained from every participant. This trial was registered with ClinicalTrials.gov of the National Institute of Health on Oct 26, 2022 (ClinicalTrials.gov No: NCT05596123).

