### Trial design

This proposed trial is a prospective, double-arm, parallel, double-blinded, randomized controlled trial. Participants, the outcome assessors, and the statistician will be unaware of the group assignment. A one-to-one ratio will help randomly assign participants to the TCFM group or the placebo massage group evenly. Six weekly 25-min TCFM sessions will be delivered to participants in the TCFM group. Six weekly 25-min placebo massage sessions will be delivered to participants in the placebo massage group. Depending on the convenience and preference of participants, the TCFM or placebo massage will be conducted either at participants' homes or in a room provided by University of Houston-Downtown. The trial will be reported following the Consolidated Standards of Reporting Trials (CONSORT) Statement (34). Figure 1 shows the enrolment, interventions, and assessment schedule of this proposed trial.

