### Statistical analysis

We will summarize the characteristics of the participants at baseline by treatment arm using descriptive statistics. Specifically, we will use mean (standard deviation) for normal (or roughly normal) continuous data, and medians (25th percentile, 75th percentile) for non-normal continuous data, and frequency (percentages) for categorical data. The two-sample *t-*test and chi-square test (or Fisher's exact test, as appropriate) will be used to examine differences by the two arms at baseline.

The primary outcome will be assessed according to intention-to-treat (48) principles. We will use a mixed model for repeated measures (MMRM) (49) to model the change from baseline at each post*-*baseline visit in two arms, with each of the primary outcomes as dependent variable. For each of the outcome, using MMRM, we will compare the difference between the treatment vs. placebo arm in change in mean response from baseline at last visit. The likelihood-based MMRM can handle missingness in the responses when the responses are missing at random (50).

For the secondary outcome, we will calculate rates of recruitment (defined as the number of consented individuals divided by the number of eligible individuals), completion (defined as the percentage of completion at baseline and follow-up visits), adherence (defined as participants' completed sessions divided by the number of offered sessions), and adverse events (in two forms, total number and number per participant).

The statistician is not part of the research team and is not aware of the group assignment. All analyses will be performed using R statistical software (version 2020) (36). A two-sided *P*-value of 0.05 or less will be considered statistical significance.

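### Both follow-up assessments are timed by treatment events (a sixth visit, completion) and not by the calendar, so participants who miss sessions or stop early have no clear outcome time under a stated intention-to-treat analysis

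*Protocol article*

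**What the plan says.** Under Primary outcome, after the baseline measurement at the first visit, the outcomes are to be "collected again at their sixth visit after the TCFM/placebo massage (immediate impact) and 12 weeks after the competition of the trial". The abstract words the same schedule differently: outcomes are "measured at baseline, end of TCFM/placebo, and twelve weeks after".

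Trial design sets the treatment schedule: "Six weekly 25-min TCFM sessions will be delivered to participants in the TCFM group", and the same number for placebo.

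Incomplete attendance is foreseen. The secondary outcomes include "No. of completed sessions, and No. of missed sessions", and Ethical approval assures participants that "they can leave the trial at any time without providing a reason". Sample size allows for 25% dropout at post-baseline visits in both arms.

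Statistical analysis states the principle: "The primary outcome will be assessed according to intention-to-treat (48) principles". The model is an MMRM on change from baseline at each post-baseline visit. The arms are compared at the last visit, and missing responses are handled under missing at random.

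**The concern.** An intention-to-treat comparison needs an outcome time that exists for every randomised participant. Here the first follow-up hangs on reaching a sixth visit and the second on completion. Someone who stops after four sessions reaches neither. Someone who reschedules may be measured later than others at the same nominal visit.

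If outcome collection follows these anchors, missing outcomes become tied to adherence. Adherence may in turn relate to discomfort or lack of benefit, and TCFM uses firmer pressure than the gentle rubbing given as placebo. Outcomes that were never collected cannot be recovered by a later analysis plan.

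**Working it through.** **1. The anchors side by side.**

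| Participant | Primary outcome section | Abstract |
|---|---|---|
| Attends all six sessions on schedule | Sixth visit, then 12 weeks after completion | End of massage, then twelve weeks after |
| Misses one session, continues | Sixth attended visit, or the sixth planned one: unclear | End of massage: unclear in the same way |
| Stops after session four | No sixth visit and no completion | Could be session four, then twelve weeks later |

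For incomplete attendance the two sections can give different outcome times, or a time in one and none in the other.

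Two further looseness points:
- Baseline is called the first visit. The sixth visit is therefore the sixth session only if massage begins at the baseline visit, which the text does not say.
- The 12-week assessment is counted from completion of the trial, but it is itself part of the trial. This is the visit at which the arms are compared.

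**2. What reaches the model.** The response is change from baseline. A participant with one post-baseline value stays in the MMRM and is handled under missing at random. A participant with none contributes no response record.

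**3. The plan's own figure.** Inputs from Sample size: power 0.80, two-sided alpha 0.05, correlation 0.8 (compound symmetry), SD of change 2, difference 1, 25% dropout.

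n per arm = 2 × φ × (z₀.₉₇₅ + z₀.₈₀)² × SD² / δ²

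- With retention 1, 0.75, 0.75 at baseline and the two follow-ups: φ = 0.64 + 0.36/0.75 = 1.12, so n = 70.33, rounded up to **71**. The stated figure is reproduced.
- With two modelled visits and retention 1, 0.75 (none missing at the sixth visit, 25% at the last): φ is again 1.12 and n is again 71.

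Under the first pattern, 0.25 × 71 = 17.75, about 18 per arm, would have baseline data only, leaving 0.75 × 71 = 53.25, about 53. Under the second, nobody would. The figure of 71 therefore does not show how many participants would lack any outcome.

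**4. Illustration of the bias.** The documents give no stopping rate and no effect for those who stop, so both are assumed: 25% stop and go unassessed, and attenders have the design effect of 1.0 point.

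Effect in all randomised = 0.75 × 1.0 + 0.25 × (effect in stoppers)

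Overstatement = 1.0 / (effect in all randomised) − 1

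| Assumed effect in stoppers | Effect in all randomised | Effect analysed | Overstatement |
|---|---|---|---|
| 0 | 0.75 | 1.0 | 33% |
| 0.5 | 0.875 | 1.0 | 14% |
| 1.0 | 1.0 | 1.0 | 0% |

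**The case against.** The case on the other side is substantial.

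- **Detail may lie elsewhere.** This is a condensed article, Figure 1 (which carries the assessment schedule) is not available, and a separate data collection protocol is mentioned. This stands: absent windows or rescheduling rules are no finding in themselves. What remains is the wording that the article does print.
- **Nominal times can be inferred.** Six weekly sessions imply a time for the sixth session and another 12 weeks later. This stands for someone who attends as planned. It does not settle the time for someone who does not.
- **Massage attendance and follow-up attendance are already counted separately.** Adherence is completed over offered sessions, and completion is defined on baseline and follow-up visits. This stands, but counting them separately does not say that those who stop will be followed up.
- **The comparison is at the last visit.** Missing the sixth visit does not by itself remove anyone from it. This also stands. However, the last visit is the one counted from completion, which a participant who stops does not reach.
- **A calendar anchor has its own price.** Someone who reschedules could be assessed before the course ends, which departs from the stated interest in immediate impact. This is a real trade-off, and it is why the fix needs a window.

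A reader might go further and infer that stopping massage ends outcome collection, so that the analysis simply is one of attenders. The documents do not support that: intention-to-treat is specified, and nothing bars assessing those who stop. A reader might also take the planned 25% as the share who stop treatment. It is dropout at post-baseline visits, that is, missing outcome data.

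**Conclusion.** The point holds as a defect in how the follow-up times are anchored. For participants who miss sessions or stop early, the printed anchors are ambiguous or never occur, and the abstract and the Primary outcome section can disagree. This fits badly with intention-to-treat and with a comparison at the last visit.

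The consequence is conditional. Only if stoppers are in fact left unassessed does the analysis lean towards attenders, and then only those with no post-baseline value are lost from the model entirely. The 0% to 33% range rests on an assumed 25% stopping rate and assumed effects in stoppers. One third is the extreme of that range and not an estimate. Different stopping rates between the arms are plausible, but the plan assumes equal dropout. The sample size of 71 per arm is reproduced and is not in question.

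**What to change.** In both the abstract and the Primary outcome section, use one definition that applies to every randomised participant whatever the attendance:
- first follow-up at the planned date of the sixth weekly session, with a window wide enough for modest rescheduling;
- second follow-up 12 weeks after that planned date.

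Add one sentence stating that stopping massage does not end outcome collection unless the participant withdraws from follow-up.

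The planned date presupposes the six weekly sessions given under Trial design. The aim at the end of the Introduction describes sessions six times a week, so these two passages must be reconciled before the dates are fixed.

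The cost is wording and a few extra contacts by the two existing outcome assessors, with home visits already foreseen. The downside is that some first follow-ups will not fall directly after a massage and so will reflect immediate impact less purely. No treatment rule changes, and 71 per arm stays.

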### Blinding

While participants, the statistician, and the outcome assessors will be blinded, the PI and the therapists will be aware of participants' group assignment. This trial is, therefore, double blinded. However, it is likely that participants will have the right guess about the type of massage they have received.

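### Adverse events are recorded only by the unblinded treating therapists, no source is named for the 12 weeks after session six, and severity is left out of the stated analysis

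*Protocol article*

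**What the plan says.** All references are to the protocol article.

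- **Who records harms.** The secondary-outcome paragraph that follows Primary outcome says "Adverse events will be recorded by the therapists in the notes". The Safety section says "The therapist will carefully document these events in the case report form", after a description of prompting: "Participants will be encouraged to verbalize experiences of increased pain, increased sensitivity in their feet".
- **Who knows the allocation.** The Blinding section says "the PI and the therapists will be aware of participants' group assignment". Participants, the statistician and the outcome assessors are blinded. The section on the therapists says that the same two people deliver both kinds of massage.
- **When.** The abstract (Outcomes) says the secondary outcomes are "measured throughout the trial process". Trial design gives six weekly sessions per arm. Primary outcome places the assessments at baseline, at the sixth visit and 12 weeks later.
- **What is analysed.** The abstract and the secondary-outcome paragraph both define the safety outcome as number and severity. Statistical analysis gives "adverse events (in two forms, total number and number per participant".
- **Related rates.** Statistical analysis also gives "completion (defined as the percentage of completion at baseline and follow-up visits", and defines adherence as completed sessions "divided by the number of offered sessions".

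**The concern.** Safety belongs to the trial's second stated aim, and the results are meant to support a claim that the massage is low-risk. The only people assigned to record harms are those who gave the massage and know which kind it was. Their scheduled contact ends with the sixth session, while follow-up runs for another 12 weeks. An event that appears after the last session, or after a participant stops attending, has no stated route into the data. Because the recorder knows the arm, the threshold for writing something down may also differ between arms, so a between-arm comparison of counts is hard to interpret.

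A total count puts a slight bruise on the same footing as one of the serious events the protocol tells therapists to watch for. Without severity, the reported result does not answer the outcome as defined.

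A smaller matter is that the completion and adherence rules can each be read in more than one way, and the readings give different rates from the same data.

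**Working it through.** **Recorder.** The secondary-outcome paragraph and the Safety section agree on the person (the therapist) and differ on the record (notes or case report form). The Blinding section makes that person unblinded. The outcome assessors appear in Blinding and Data collection, but neither section, nor any other, gives them a task on adverse events. The therapist is therefore the sole stated source.

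**Time covered.** Assume one session a week, as in Trial design, and 12 weeks counted from the sixth session. (The Introduction words the session frequency differently, and the two need to be reconciled.)

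- First to sixth session: 5 intervals of one week = 5 weeks.
- First session to last assessment: 5 + 12 = 17 weeks.
- Share with no named source of adverse events: 12/17 = 0.71, or 71%.

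This is a share of calendar time, not of risk. The Ethical approval and Safety sections both expect mild effects that may arise after a session as well as during it, so the period after session six is not empty of expected events. It need not carry the same risk per week as the treatment period.

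**Direction and size of any bias between arms.** Neither can be calculated. The documents give no event rates and no detection probabilities.

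**Severity.** The outcome has two parts, number and severity. The analysis has two forms, an overall count and a count per participant. Both forms address number; neither addresses severity.

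**Completion.** The only dropout figure is the 25% at post-baseline visits in Sample size. That calculation reproduces. With SD 2, difference 1, power 0.8 and two-sided 0.05, the unadjusted size is 2 × [2 × (1.960 + 0.842)/1]² = 62.8 per arm. With correlation 0.8 and 75% retained, the variance factor is 0.64 + 0.36/0.75 = 1.12, and 62.8 × 1.12 = 70.3, rounded up to 71 as stated. Applying the dropout to the completion rule gives:

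| Dropout | Three visits pooled, (1 + 2 × (1 − d))/3 | Follow-up visits only, or all visits required |
|---|---|---|
| 10% | 93.3% | 90% |
| 25% (planned) | 83.3% | 75% |
| 40% | 73.3% | 60% |

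Reported separately for each visit, the 12-week figure is also 75% at the planned dropout. Only pooling raises the rate, by 8.3 percentage points at 25%.

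**Adherence.** Six sessions are planned for everyone. If the offered sessions always number six, a participant who leaves after two scores 2/6 = 33% and nothing is inflated. If offers stop at withdrawal, the same person scores 2/2 = 100%. As an illustration, assume that 25% withdraw after session three and everyone else attends all six. Completed over planned is (0.75 × 6 + 0.25 × 3)/6 = 87.5%, against 100% for completed over offered. Moving the withdrawal from after session one to after session five moves the planned-session figure from 79.2% to 95.8%.

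**The case against.** The best defence is that harms collection is better than one line about notes suggests. Participants are prompted for a list of symptoms at sessions, the therapist assesses reactions, and a case report form is used. That stands, and it means reporting is not left wholly to chance during treatment. It does not change who records, what that person knows, or what happens after session six.

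A second objection is that a condensed article may leave follow-up harms collection and severity tables to the full protocol or analysis plan. This has some force as to detail. But the article does fix the recorder, does say that the outcome is measured throughout, and does fix the analysis in two forms. Those statements do not fit together as written.

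A reader might infer that knowledge of the arm makes the therapists under-record harms of the active massage. The documents do not support a direction. The same therapists treat both groups, and they could equally look harder for events under the firmer technique.

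A reader might also infer that the completion and adherence rules are built to flatter the trial. That is not shown either. Completion rises only if three visits are pooled, which the text does not say. Adherence rises only if the offered number falls below six, which the text does not describe. Withdrawals, missed sessions and the number finishing in their assigned group are reported separately, so attrition stays visible. On these two rates the objection largely succeeds, and what remains is a request for clearer wording.

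Finally, asking about soreness or bruising may hint at the allocation to a blinded assessor. That is a real cost of the remedy and determines the order of questions proposed below.

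**Conclusion.** The point holds for adverse events. The sole stated recorders are unblinded, no source is named for 12 of 17 weeks, the two places that describe the record disagree, and severity is in the outcome but not in the analysis. Later events can be missed, and ascertainment can differ between arms in an unknown direction and by an unknown amount. The 17 weeks rest on the weekly schedule.

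Completion and adherence warrant a clarification only. The gap of 83% against 75% arises on one reading at the planned dropout, and adherence is affected only if the offered sessions can number fewer than six. The wider conclusion that all the secondary-outcome rules err in the trial's favour does not follow from the text.

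Nothing here touches the sample size or the primary analysis. It is a worthwhile, inexpensive improvement to the second aim.

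**What to change.** 1. Keep the therapist records, and state whether they are held in the notes, the case report form or both.
2. Have the blinded outcome assessors ask every participant one fixed adverse-event question at the sixth-visit and 12-week assessments. Ask it after the primary outcome questionnaires are complete, so that an answer which reveals the allocation cannot affect those scores at that visit.
3. Report the number of participants with at least one event, by arm and by severity, alongside the two counts already planned.
4. As a clarification, define completion as the proportion of randomised participants with a 12-week assessment, and adherence as completed sessions divided by the six planned for every randomised participant.

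The cost is one question at each of two existing assessments and a few reworded sentences, with no new visits or staff. The downsides are slightly longer assessments and some risk of unmasking the assessor. Because answers at the sixth visit could carry over to the 12-week assessment, the order of questions limits that risk but does not remove it.
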